#### Description of the patient groups at baseline

The baseline features of the patients will be described with descriptive statistics using absolute numbers (*n*) and percentages for categorical variables and the minimum, maximum, mean, SD and quartiles for quantitative variables. The number of patients crossing over to surgical treatment or dropping out from follow-up will be documented.

#### Analysis of the primary outcome

Multiple regression analysis of subgroup factors will allow for the determination of important factors affecting the NDI. The differences will be considered statistically significant if the *p* value is less than 0.05.

### Analysis of the secondary outcomes

#### EQ-5D

HRQoL will be evaluated with the EQ-5D by comparing the results from the two groups, using the independent *t* test, the Mann-Whitney *U* test or the Fisher exact test.

The differences will be considered statistically significant if the *p* value is less than 0.05.

### Non-union

A chi-squared test will be used to compare the non-union rate between the two groups.

### VAS

The VAS will be evaluated using the *t* test, the Mann-Whitney *U* test or Fisher’s exact test.

### Survival

The Kaplan-Meier method will be used for the determination of the non-surgical and surgical treatment mean survival at 1 year. Proportional survival differences according to treatment will be tested with the chi-squared test. With the Cox proportional hazards regression method, covariates contributing to survival will be entered in univariate and multivariate models, if the hazard ratio presents with a 95% confidence interval (CI).

#### Subgroup analysis

We will perform a separate analysis of participant socio-demographics, type-2 odontoid fracture subgroup, the specific type of surgery (categorical: Magerl-Atlas claw or Goel-Harms) and osteoporosis status (DXA score).

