### Statistics

For statistical analysis, R version 3.4.1 (R Foundation for Statistical Computing, Vienna, Austria) will be used. The results will be presented according to the CONSORT Statement for non-pharmacological interventions [26]. The analysis will be performed by intention-to-treat (ITT), and sensitivity analyses will include a per-protocol analysis.

Missing values will be imputed using multiple imputation by use of chained equations as implemented in the R package “mice” with 20 iterations [40]. Details of the statistical analysis are listed in Table 1.

**Table 1 Tab1:** Variables, measures and methods of analysis

Variable/Outcomes	Hypothesis	Outcome measures	Methods of analysis
*Baseline data:*	There is no difference between the two groups	Gender, age, Katz ADL, CCI, nursing home/hospitalisation, smoking status	Absolute numbers, percentages for categorical variables and the minimum, maximum, mean, SD and quartiles for quantitative variables
*Primary:*			
Function	There is a clinically important difference between the two groups, with improvement comparing baseline data with data from 6 weeks, 12 weeks, and 1 year. Surgical treatment is hypothesised to be superior	NDI (0–100%) [continuous]	Student *t* test, chi-square, Mann-Whitney, Fisher’s exact test. Time-dependent differences between AUC
*Secondary:*			
Health-related quality of life	There is a clinically important difference between the two groups	EQ-5D [continuous]	Student *t* test, chi-square, Mann-Whitney, Fisher’s exact test Time-dependent differences between AUC
Pain	There is a clinically important difference between the two groups	VAS (0–100) [continuous]	Students *t* test, chi-square, Mann-Whitney, Fisher exact test Time-dependent differences between AUC
Non-union	The non-union rate is lower in the surgical group	Bone bridge in CT [binary], mobility on extension-flexion radiographs [binary],	Chi-square test
Mortality	The survival is greater in the surgical group	all-cause mortality [binary], time to death [continuous, censored]	Kaplan-Meier analysis, Cox regression models, additional subdistribution hazards approach
Osteoporosis	There is no difference between the two groups	The bone density is > 2.5 standard deviations below normal DXA T-score [binary]	Chi-square
*Subgroup analysis:*			
septuagenarians vs. octogenarians vs. nonagenarians	Treatment effect is diminished in nonagenarians		
Goel-Harms technique vs. Magerl technique	There is no difference between the two groups		

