### Sample size

Up to 50 participants will be included in the study, based on the following calculation of sample size:

The MCID of the NDI is 3.5 points (7%) and the SD is 3.5 points [28]. Thus, 16 participants are needed in each group to reach 80% power with a two-sided significance level of *p* < 0.05 in a (clinically important) superiority study design. Adjusting for 1-year mortality among those aged ≥ 70 years with a non-surgical axis fracture treatment of 29% (Robinson AL et al. Spine J. 2018; in press), eight additional participants must be recruited in each group. A minimum of 24 subjects must be included in each group.

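### Table 1 hypothesises a smaller treatment effect in nonagenarians, but the only subgroup method stated is a separate analysis, which does not compare effects between age groups

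*Protocol article*

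**What the plan says.** Table 1 (Statistics) has a subgroup row "septuagenarians vs. octogenarians vs. nonagenarians" with the hypothesis "Treatment effect is diminished in nonagenarians". Its cells for outcome measure and method of analysis are empty, as they are in the rows for surgical technique and sex, where the hypothesis is no difference.

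The method appears only under Subgroup analysis, within Analysis of the secondary outcomes: "We will perform a separate analysis of participant socio-demographics". The sentence goes on to fracture subgroup, specific type of surgery and osteoporosis status.

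Two other places use related factors. Analysis of the primary outcome plans a multiple regression on the subgroup factors to identify what influences the NDI. The sensitivity rows of Table 1 list covariate-adjusted logistic and Cox models. Neither mentions a treatment-by-factor term.

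**The concern.** A hypothesis that an effect is smaller in one group concerns the difference between two effects. Analysing each group on its own gives two effects and no test of their difference. The usual shortcut is to note that one p value is below 0.05 and the other is not. That mostly reflects how many patients each group holds, and a 90+ stratum in a trial of at most 50 patients is likely to be small.

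The error would also run in the direction that the investigators expect, so a reader is less likely to question it. At stake is a statement that the oldest patients gain less from surgery, made from data that cannot show it.

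**Working it through.** **Inputs from the article.** Sample size: "The MCID of the NDI is 3.5 points (7%) and the SD is 3.5 points", so the planned effect is 1 SD; "a two-sided significance level of *p* < 0.05"; "16 participants are needed in each group to reach 80% power"; 29% one-year mortality; up to 50 participants. Sequence generation: simple randomisation.

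**Assumed, because the article does not give it.** The number of nonagenarians among evaluable patients. A range is shown.

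**The plan's own figure.** n per group = 2 × (1.96 + 0.84)² × (3.5/3.5)² = 15.7, so 16. Exact t-test power is 78.1% at 16 per group and 80.7% at 17. The mortality allowance gives 16/0.71 = 22.5 and 17/0.71 = 23.9, against the stated 24. The planning figure is reproduced closely enough. Evaluable at one year: 50 × 0.71 = 35.5, taken as 36.

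**Two groups (younger vs 90+), near-equal arms, same 1-SD effect at every age, 36 evaluable.** With noncentral-t power in each group, P(pattern) = P(younger significant) × P(90+ not significant):

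- 10% nonagenarians (4 vs 32): 0.781 × 0.909 = 0.71
- 20% (7 vs 29): 0.737 × 0.813 = 0.60
- 30% (11 vs 25): 0.667 × 0.685 = 0.46

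Under simple randomisation these become 65%, 56% and 46% of the trials in which the 90+ group can be tested.

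**Three decades as in Table 1, simulated with coin-flip allocation, 36 evaluable.** The pattern is at least one younger decade significant and 90+ not. A stratum of n patients has fewer than two in some arm with probability 2(1 + n)/2ⁿ.

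| 75-79 / 80-89 / 90+ | 90+ untestable | Pattern at 1 SD, untestable counted as non-significant | Pattern at 1 SD with a testable 90+ stratum, of all trials | Pattern at 0.5 SD, untestable counted as non-significant |
|---|---|---|---|---|
| 12 / 20 / 4 | 10/16 = 62.5% | 66-68% | 23% | 26% |
| 10 / 20 / 6 | 14/64 = 21.9% | 57-58% | 43-44% | 24-25% |
| 10 / 18 / 8 | 18/256 = 7.0% | 50% | 46% | 23% |
| 8 / 17 / 11 | 24/2048 = 1.2% | 40% | 40% | 20% |

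At 10/20/6 and 0.75 SD the figure, counted as in the third column, is 41%.

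**Interaction test (nonagenarian vs younger, two-sided 0.05), same uniform effect.** It is falsely significant in about 5% of trials in either direction and in about 2-3% in the stated direction.

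**Power of that test** if the effect were 1 SD in younger patients and zero in nonagenarians, for shares of 10-30%: about 15-27% with 36 evaluable and 17-35% with 50.

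**The case against.** **The wording is ambiguous.** A separate analysis may mean only separate from the primary one. No within-stratum test, p value or decision rule is stated, and a full protocol or SAP, not shown, could name an interaction test. This stands against any claim that the plan says it will compare significance across strata; a reader might infer that, but the text does not say it. It does not remove the mismatch: the article states a directional hypothesis and the approach to subgroups, and that approach as worded is not a comparison of effects.

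**There is also a regression on subgroup factors.** True, but as worded it looks for factors that affect the NDI, which is prognosis. The adjusted models are described no further.

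**The false pattern need not be usual.** A reader might infer that separate tests would usually confirm the hypothesis. The figures do not support that. At 10/20/6 the pattern falls to 48% if only octogenarians are set against 90+, and to 12% if both younger decades must be significant. If only the point estimates are compared, nonagenarians look worse in about 50% of trials. Part of the higher figures comes from strata that cannot be tested at all.

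**Other factors.** Extending the same false confirmation to sex, ASA class or osteoporosis is not supported. For sex the stated hypothesis is no difference, and for ASA class and for osteoporosis as a subgroup factor no effect-modification hypothesis is stated.

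**Importance.** The primary conclusion is untouched, and the Discussion ties guidelines to the trial's key results, not to its subgroups. Both points stand and limit the weight of this one.

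**Conclusion.** The point holds in a limited form. The article pairs a pre-specified effect-modification hypothesis with a method that, as stated, cannot test it, and no section plans a comparison of effects between age groups.

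The size is conditional on the hypothesis being judged from within-stratum tests. With 36 evaluable patients and a uniform 1-SD effect, the false pattern arises in roughly 40-70% of trials over the assumed nonagenarian shares, counting untestable 90+ strata as non-significant. At 0.5 SD it arises in about 20-26%. The word for this is often, not usually. On that same count, each of these values is far above the 2-3% of an interaction test in the same direction. The calculation assumes normal outcomes with the planning SD and 29% loss to death in both arms.

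**What to change.** For factors defined in both arms (age, sex, BMI, ASA class, smoking, fracture subgroup, osteoporosis), replace the separate analyses with one model per factor: 12-month NDI on treatment, factor and treatment-by-factor interaction, adjusted for baseline NDI. Keep age continuous and show the estimated treatment effect at a few chosen ages. Report each interaction estimate with its 95% CI, draw no conclusion from within-stratum p values, and label the results exploratory. Enter this in the empty method cells of Table 1.

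Leave type of fusion out of this scheme. It is defined only for operated patients, so no treatment interaction can be estimated. Present it as a descriptive, non-randomised comparison among them.

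The cost is wording only; no extra data or patients are needed. The downside is low power, about 15-35% for the nonagenarian contrast computed above (a continuous-age term will differ somewhat). The age hypothesis will probably be reported as inconclusive, which is what a trial of this size can support.

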### Sample size

Up to 50 participants will be included in the study, based on the following calculation of sample size:

The MCID of the NDI is 3.5 points (7%) and the SD is 3.5 points [28]. Thus, 16 participants are needed in each group to reach 80% power with a two-sided significance level of *p* < 0.05 in a (clinically important) superiority study design. Adjusting for 1-year mortality among those aged ≥ 70 years with a non-surgical axis fracture treatment of 29% (Robinson AL et al. Spine J. 2018; in press), eight additional participants must be recruited in each group. A minimum of 24 subjects must be included in each group.

### Monitoring

#### Data monitoring

An interim analysis will be performed on the primary endpoint (NDI improvement) when 30 patients have been randomised and completed the 1-year follow-up. The interim analysis will be performed by a statistician. The statistician will report to the R&D Council of the Orthopaedic Department at Uppsala University Hospital (FoUU rådet). The R&D Council will have unblinded access to all data. The council, which will decide on the continuation of the trial, will report to the Central Ethics Committee if the trial is stopped prematurely [41]. The decision regarding study discontinuation follows the Haybittle-Peto stopping rule: if treatment effects cause an NDI improvement difference between surgical and non-surgical groups with *p* < 0.001 in the interim analysis, the trial will be stopped [42].

#### Harm

If the attending physician suspects a serious adverse event (SAE), the patient’s follow-up will not be discontinued. An SAE is considered if it results in the following outcomes: in-hospital death, life-threatening event or neurological worsening. In case of severe adverse advents, the investigator in charge of the study will inform the R&D Council. The council will then decide on whether to continue the trial, reporting to the Central Ethics Committee if the trial is stopped prematurely.

#### Auditing

The SweSpine board (governed by the Swedish Society of Spinal Surgeons) reviews the patient-reported outcome measure forms and clinical data at regular intervals.

### Ethics and dissemination

#### Research ethics approval

This study is conducted in compliance with the current version of the Declaration of Helsinki. The research project was approved by the Uppsala Regional Ethics Committee on 18 May 2011 (registration no. 2011/068).

#### Protocol amendments

Modifications to the protocol require approval by the Regional Ethics Committees, will be registered with ClinicalTrials.gov, and will be communicated to the participating university hospitals.

#### Consent or assent

Prior to the trial, patients must consent orally and in writing after the possible consequences of the clinical study are explained in an understandable way. All documents must be written in Swedish. If the patient is unable to give informed consent, a close relative will be asked to take the decision instead. The patient will receive a copy of the signed patient information. A patient may withdraw from the study at any time if they are unwilling to continue on the trial. In this case, the data from a patient who requests full withdrawal will not be considered in the data analysis.

#### Confidentiality

All original documents will be kept in the clinical research unit for the next 15 years. The study data will be handled in line with by the European Directive 95/46/EC on data protection. All original records will be kept on file at the trial sites or coordinating data managing centre for 10 years. The electronic clinical trial database in SweSpine will be kept on file for at least 10 years.

#### Access to data

The principal investigators have full access to the final datasets. There are no contractual agreements that limit such access for investigators.

#### Dissemination policy

The study results will be published in peer-reviewed medical journals, and communicated at medical conferences. The original principal investigators AR, YR and CO will appear as co-authors on all publications based on results from this study cohort. The participant-level dataset and the statistical code will not be publicly available and remain with the principal investigators.

## Discussion

This is the first randomised controlled study on the treatment of type-2 odontoid fractures in the elderly. The key results of this study will be applicable to evidence-based guidelines and benefit the growing elderly population.

Since surgery among the elderly is associated with a 4-day longer hospital stay, the results of this randomised controlled trial (RCT) will have direct implications on health policy and medical decision-making (unpublished data).

Function and HRQoL are important pillars of value-based care. Thus, this study uses a functional patient-reported questionnaire as its primary endpoint. We discarded mortality as the primary endpoint due to the fragility of patients above 70 years of age, where hazard causes overlap and sample size issues arise [43].

### Limitations

This randomised controlled study employs an open-label design, where both the investigator and the patient know which treatment they will receive. Unfortunately, the open-label design has an inherent selection bias, where patients can drop out during enrolment or give informed consent prior to inclusion in this study.

A review of the allocation concealment methods of major medical journals in 2015 found that 19% of trials involved an inadequate allocation method and 22% were without appropriate reporting of the randomisation method [44]. Our protocol uses SNOSE allocation concealment and simple randomisation. The sealed envelope technique requires good clinical practice and discipline of the part of the enrolling physician, since translucency and premature opening can corrupt the randomisation process [45]. Simple randomisation avoids deciphering block randomisation but risks different sample sizes in treatment and control groups. Transparency of the randomisation process and close supervision of the randomisation process by the principle investigator and the R&D Council will control the quality of this RCT.

One-year progression-free survival and 1-year all-cause mortality are common primary endpoints for RCTs. Due to the frailty of the elderly study participants, an overlap of an unrelated and natural cause of death with injury-related mortality causes high variation and would require a significantly greater sample size. Since HRQoL defines the value of life years gained, this study uses the NDI as the primary endpoint, with EQ-5D and survival as secondary endpoints.

We have planned to deal with dropouts for death in our sample size calculation, adopting an inflation rate. However, death will represent an important competing event. It is possible that if surgery has a favourable impact on mortality, more people will die in the control group, and earlier. These people who die might be those more compromised. This means that people in the control group who survive at 1 year might be those who are healthier, which might dilute the actual effect of the intervention on disability. To adjust for competing events we aim to use a subdistribution hazards approach to adjust for mortality [46].

The results from this study will provide overdue evidence regarding the treatment of type-2 odontoid fractures in the elderly. The QALYs gained with optimal treatment will support policy-makers and clinicians with their informed decisions.

### Trial status

This protocol been approved and registered with the Uppsala Regional Ethics Committee on 18 May 2011(no. 2011/068). It was registered retrospectively with ClinicalTrials.gov on 25 August 2015 (NCT02789774; pre-results). Patient inclusion for USOFT started in February 2012 in the Department of Surgical Sciences at Uppsala University Hospital, Uppsala, Sweden, and in October 2014 in the Department of Spine Surgery at Malmö University Hospital, Malmö, Sweden. Inclusion of other departments over the course of time is planned. Recruitment is planned to be completed before 31 December 2018.

## Abbreviations

ADL: Activities of daily living
ASA: Classification according to the American Society of Anaesthesiologists
BMI: Body Mass Index
C: Cervical vertebrae
CCI: Charlson Comorbidity Index
CI: Confidence interval
CONSORT: Consolidated Standards of Reporting Trials
CT: Computed tomography
DXA: Double x-ray absorptiometry
EQ-5D: EuroQol group questionnaire
HR: Hazard ratio
HRQoL: Health-related quality of life
ICD-10: International Classification of Diseases
ITT: Intention-to-treat
IV: Intravenous
MCID: Minimal clinically important difference
NDI: Neck Disability Index
NPR: National Patient Registry (patientregistret, Socialstyrelsen)
OR: Odds ratio
R&D: Research and development
RCT: Randomised controlled trial
RR: Risk ratio
RRR: Relative risk reduction
SAE: Serious adverse events
SCI: Spinal cord injury
SNOSE: Sequentially numbered, opaque sealed envelope
SPSS: Statistical Package for the Social Sciences
SweSpine: Swedish Spine Registry
USOFT: Uppsala Study on Odontoid Fracture Treatment
VAS: Visual Analogue Scale
